## Abstract

**Background/Objectives**: Dementia involves progressive cognitive and functional deterioration that leads to dependence and overload on family caregivers. This overload has a negative impact on the physical, mental, emotional, and occupational health of caregivers, leading to occupational imbalance and problems arising from an inadequate distribution of time devoted to caregiving. This project aims to evaluate the effects of the technology-based CAREFIT programme, structured around physical activity interventions, education, and psychoemotional and social support, on the health-related quality of life and emotional well-being of informal caregivers. **Methods**: The experimental group will develop the intervention programme, which will last 8 weeks and combine educational activities, physical activities, and psychoemotional and social support. Before beginning the intervention, the entire experimental group will receive a training session and educational materials on how to access and use the platform. The CAREFIT platform will consist of two educational sessions and two weekly physical sessions, combined with psychoemotional and social support activities that participants must complete. Initial, final, and follow-up evaluations will be conducted. The HRQoL and psychoemotional health (stress, anxiety, depression, and perceived social support and burden) of caregivers of people with dementia will be the main outcome measures. The effects of the intervention on the study variables will be assessed using a repeated-measures analysis of variance (ANOVA). **Conclusions**: The proposed protocol for the CAREFIT programme represents an innovative and multidisciplinary initiative that leverages a digital platform to promote the well-being of informal caregivers of people with dementia. This approach combines health literacy and strengthened psychoemotional and social support. Through this integration, the goal is to reduce the levels of burden, stress, anxiety, and depression among primary caregivers, while strengthening their self-care capabilities and social support networks.

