To the best of our knowledge, there have been studies that intervened through psychoeducational [27,28] or cognitive–behavioural [29,30] programmes for caregivers of people with dementia or publications on didactic exercise interventions in people with dementia and their caregivers [31,32], as well as some educational, psychoemotional, and physical interventions whose medium of application was the internet [24]. In addition, there is evidence that programmes including educational modules, forums and real-time support sessions [33], and eHealth psychoeducational programmes aimed at increasing knowledge of neurocognitive disorders, their management at home, and the presence of national support services [34] have significantly reduced the level of behavioural symptoms in patients with dementia, increased empowerment, and eased the burden on caregivers, thus improving their caregiving skills. There are even interventions that have evaluated the effectiveness of an online psychoeducational programme combined with an immersive virtual reality (VR) experience in reducing caregivers’ perceived stress by acting on the cognitive and affective components of empathy [35]. However, there is no study that has used technological means to carry out an interdisciplinary programme with PA interventions together with health literacy for informal caregivers of people with dementia. Therefore, the aim of this project is to determine the effect of an 8-week intervention programme based on the CAREFIT (Caregivers’ Active Resilience & Exercise for Fitness and Well-being) programme on the HRQoL and psychoemotional health (stress, anxiety, depression, and perceived social support and caregiver burden) of caregivers of people with dementia.

In this sense, the hypothesis of the study protocol is that the implementation of an 8-week intervention programme based on the CAREFIT model will improve health-related quality of life (HRQoL) and psychoemotional health indicators (decreased stress, anxiety, depression, and overload, as well as increased perceived social support) in caregivers of people with dementia, compared to those who do not participate in the programme.

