#### 2.2.3. Sample Calculation

The calculation of the number of participants needed for this study was based on the expected change in quality of life as measured by the EQ-5D-5L questionnaire. Since, to our knowledge, there are no specific data on the minimum clinically relevant change in informal caregivers using this instrument, a minimum difference of 0.07 units was taken as a reference value [39]. Considering a significance level (alpha) of 0.05 and a statistical power greater than 0.8 in a two-sided test, it was determined that 25 participants in the control group and 25 in the experimental group are needed to identify a difference equal to or greater than 0.07 units as significant. A common standard deviation of 0.12 [40] and a correlation coefficient of 0.8 between the initial and final measurements were assumed. In addition, an estimated dropout rate of 25% was calculated. The calculation was performed using version 7.12 of the GRANMO to determine the sample size. (https://www.datarus.eu/aplicaciones/granmo/ (accessed on 10 January 2025)).

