#### 2.2.7. Statistical Analysis

The data will be analysed with the computer programme IBM Social Sciences (SPSS, version 25.0, Armonk, NY, USA). The normality and homogeneity of the data will be examined by Levene and Kolmogorov–Smirnov tests, respectively. The baseline and socio-demographic characteristics of the study participants will be presented for categorical variables as frequencies and percentages and for continuous variables as means and standard deviations.

The effects of the intervention on the study variables, HRQoL, physical condition, and psychoemotional state (stress, anxiety, depression, caregiver strain, and perceived social support), will be assessed by repeated-measures analysis of variance (ANOVA). The results of the study will incorporate the effect size, together with its corresponding 95% confidence interval, as well as the statistical significance for each measure analysed, considering both the evolution over time and the interaction effects between group and time. If the data do not follow a normal distribution, the Friedman test will be applied. Statistical significance will be established at the conventional level of *p* < 0.05.

In the case of missing data, the Intention-To-Treat (ITT) strategy will be used to maintain the original randomisation and reduce the risk of bias by analysing all participants according to the group to which they were assigned, regardless of their level of adherence.

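### Six outcome domains share the rank of main outcome at one 0.05 threshold, while only EQ-5D-5L was powered and no rule says which result counts as success

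*Protocol article*

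**What the plan says.** The Abstract puts HRQoL first and adds that "psychoemotional health (stress, anxiety, depression, and perceived social support and burden) of caregivers of people with dementia will be the main outcome measures". The aim at the end of the Introduction names the same set, "HRQoL and psychoemotional health (stress, anxiety, depression, and perceived social support and caregiver burden) of caregivers of people with dementia", and gives no order of importance. The hypothesis that follows also covers the whole set, as a comparison with caregivers who do not take part.

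Section 2.2.3 sizes the trial on one instrument. The calculation "was based on the expected change in quality of life as measured by the EQ-5D-5L questionnaire", with a difference of 0.07, a standard deviation of 0.12 and a correlation of 0.8 between the initial and final measurements. Its error rates are given as "Considering a significance level (alpha) of 0.05 and a statistical power greater than 0.8 in a two-sided test".

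Section 2.2.7 applies the same model to every outcome: "HRQoL, physical condition, and psychoemotional state (stress, anxiety, depression, caregiver strain, and perceived social support), will be assessed by repeated-measures analysis of variance (ANOVA"). It will report an effect size and its 95% CI, "as well as the statistical significance for each measure analysed, considering both the evolution over time and the interaction effects between group and time". The threshold is set once: "Statistical significance will be established at the conventional level of" p < 0.05.

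Section 2.2.6 shows that some domains yield more than one score. EQ-5D-5L gives a dimension profile, a visual analogue scale and an index. Depression is measured by a GHQ-12 subscale and again by the GDS. No score is preferred over another.

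**The concern.** The outcome hierarchy and the sample size do not match. One outcome was used to size the trial, but six domains carry the same rank and face the same threshold. The article never labels EQ-5D-5L as primary and never says what pattern of results would show that the programme works.

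This matters because the Discussion and Conclusions tie wider use in public services and care policy to the programme proving effective. As written, a significant result on one unpowered scale could be presented as that proof even if EQ-5D-5L showed nothing. The point concerns the equal ranking that the article states. It is not that a multiplicity procedure is missing, which could sit in an analysis plan that is not shown.

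**Working it through.** **1. The plan's own figure.** Inputs from section 2.2.3: difference 0.07, SD 0.12, correlation 0.8, two-sided alpha 0.05, power 0.80, dropout 25%.

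- SD of the change score: 0.12 × √(2 × (1 − 0.8)) = 0.0759.
- Completers per arm: 2 × (0.0759 × (1.960 + 0.842) / 0.07)² = 18.45, so 19.
- With dropout: 18.45 / 0.75 = 24.6, so 25. Rounding to 19 first gives 19 / 0.75 = 25.3, so 26.

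The stated 25 per arm therefore reproduces as a between-group comparison of change from initial to final EQ-5D-5L. By normal approximation, power is 81.1% with 19 completers per arm and 90.3% with 25. The difference of 0.07 and SD of 0.12 point to the index, although section 2.2.3 says only units of EQ-5D-5L.

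**2. How many tests.** There are six domains: HRQoL, stress, anxiety, depression, social support and burden. Section 2.2.6 gives at least eight scores within them: EQ-5D-5L index, EQ VAS, PSS, GHQ-12 anxiety, GHQ-12 depression, GDS, ZBI and Duke-UNC-11. I take one group-by-time test per domain (k = 6) or per score (k = 8).

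**3. Chance of at least one false positive, if any one significant result counts as success.** All nulls are taken as true and each test is two-sided at 0.05.

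- Independent tests: 1 − 0.95⁶ = 0.265 and 1 − 0.95⁸ = 0.337.
- Correlated tests: simulation of k equally correlated z-tests, 1,000,000 draws. The document gives no correlations between outcomes, so these are assumptions shown as a range.

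| Assumed correlation | 6 tests | 8 tests |
|---|---|---|
| 0 | 26.5% | 33.7% |
| 0.5 | 20.7% | 25.0% |
| 0.7 | 16.4% | 19.1% |
| 0.8 | 13.8% | 15.7% |

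**4. If all main outcomes must be significant.** Type I error is then not inflated, but joint power cannot exceed the power for EQ-5D-5L, about 81% with 19 completers per arm. As an illustration, six independent outcomes each with 80% power give 0.8⁶ = 26%. Positive correlation would raise that figure. The article calculates power for EQ-5D-5L only.

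**5. What each repair costs in participants.** One primary outcome, EQ-5D-5L, leaves alpha at 0.05 and the sample at 25 per arm. Keeping the outcomes co-equal under a Bonferroni correction, on the EQ-5D-5L assumptions, needs 29 completers per arm at 0.05/6 or 31 at 0.05/8. With 25% dropout that is 29 / 0.75 = 38.7, so 39 per arm, or 31 / 0.75 = 41.3, so 42 per arm.

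**The case against.** Section 2.2.3 does single out an instrument, a difference and a before-after contrast, so a sympathetic reader could take EQ-5D-5L as the implied primary outcome. On that view only a label is missing. This largely stands, and it is why the repair is cheap. It does not remove the conflict, because the Abstract and the aim give five other domains equal rank.

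The any-one-is-enough rule is also an assumption. Section 2.2.7 does not say that a single significant result means success, and the hypothesis can be read as requiring improvement throughout. That too stands, so the error figures must be stated conditionally.

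Three stronger readings are tempting, and the article does not support them:

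- A reader might infer that the false-positive risk simply is 20-34%. The upper end needs eight independent scores, which is implausible when two scales measure depression, two scores come from one GHQ-12, and EQ-5D-5L has its own anxiety/depression dimension. It also assumes that EQ VAS and the index are each tested, whereas section 2.2.7 says only HRQoL.
- A reader might infer that success could be claimed at whichever visit looks best. Section 2.2.7 plans a repeated-measures model with one group-by-time test per measure across the three assessments, and describes no visit-by-visit testing.
- A reader might count the time effects as further chances of a false claim. The hypothesis is a between-group comparison, and a change over time common to both arms does not bear on it.

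**Conclusion.** The point holds in a limited form. The article fixes six co-equal main outcomes and one threshold for each measure, sizes the trial on one of them, and leaves open which result would count as success. Under an any-one rule with all nulls true and one group-by-time test per domain or score, the false-positive chance is about 21-26% for six tests and 25-34% for eight at assumed correlations of 0.5 to 0. At 0.7-0.8 it is about 14-19%, still roughly three times the nominal 5%. Under an all-required rule the error is controlled, but the power is unknown. Either way the plan needs a stated primary outcome. This should be fixed as a cheap improvement. It is not a fault in the sample size, the data collection or the choice of model.

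**What to change.** Name one primary outcome that matches section 2.2.3: the between-group difference in change in EQ-5D-5L index from baseline to week 8, tested at two-sided 0.05. Say in section 2.2.7 that this contrast is the primary test, since the group-by-time interaction described there spans all three assessments.

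Label stress, anxiety, depression on one named scale, burden and social support as secondary. Label EQ VAS, the other depression scale, the week-12 results and occupational balance as secondary or supportive. Report these with 95% confidence intervals, or apply a stated multiplicity adjustment if p-values are to support claims. Bring the Abstract, the aim and section 2.2.7 into line, and check that the registration mentioned in section 2.2.2 agrees.

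The cost is wording. Sample size, alpha, instruments and visits stay as they are. The one real loss is that the psychoemotional outcomes can no longer each carry a confirmatory claim at 0.05. If the investigators want to keep that, they need either an adjusted threshold, at about 39 to 42 per arm on the Bonferroni figures above, or an explicit all-required rule with its joint power calculated.

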## 1. Introduction

The increase in the life expectancy of the world’s population and the risk of dementia are growing proportionally. As people age, the likelihood of developing dementia increases, which, in turn, leads to a greater demand for care by older people, especially in Western industrialised countries [1]. Today, an estimated 47 million people worldwide suffer from dementia [2]. The prevalence of dementia increases by approximately 5% for every 5-year increase in age, and is more pronounced in women due to their greater longevity [3].

Dementia is an acquired syndrome characterised by a set of symptoms that result in the persistent impairment of cognitive functions and impaired functional ability in people who do not suffer from impaired consciousness [4]. Dementia, therefore, causes a gradual loss of self-care capacity and increases, over time, the need to receive help from a caregiver to carry out activities of daily living (ADLs). The situation of dependency of the patient with dementia generates a state of overload in the caregiver, who assumes a complex and demanding role. This situation has a significant impact on the caregiver’s health, producing a series of negative consequences [5,6]. In this regard, care for dementia patients falls mainly on family caregivers [7,8]. This role is marked by gender, with women being the main caregivers [9], and also by age, a particularly relevant factor since, in most studies with caregivers, participants are around 65 years of age on average [9,10] and can even reach 77 years of age [11].

The complexity of caring for a patient with dementia generates a significant overload on the caregiver, affecting their physical, mental, and emotional health. The role of the caregiver can generate an overload that negatively affects the occupational performance of informal caregivers, understood as the person’s ability to carry out ADLs (self-care, education/work, play/leisure, social participation, and rest), and instrumental ADLs (those related to caring for others, the home, and the community) [12,13]. One of the consequences or situations of occupational injustice that the informal caregiver may experience is occupational imbalance, which is related to an inadequate distribution of time spent in different occupations. In this context, this involves spending too much time in one area of life and neglecting others, which can lead to various health problems [14].

Therefore, it is especially necessary to design and implement interventions that enable carers to develop strategies and skills to more effectively face the challenge of caregiving, as well as to improve stress management, time management, and access to resources and support services, fostering active ageing and a better quality of life, preparing them to face the physical and mental demands of caregiving and prevent chronic diseases. Furthermore, these interventions should be oriented towards the creation of social and emotional support networks where carers can share experiences, receive advice, and feel more accompanied or supported in their task. Therefore, interventions related to active ageing and quality of life in informal carers of people with dementia are essential to promote their physical, mental, and social well-being and are a necessary investment to ensure the well-being of this population group and contribute to a more sustainable and equitable dementia care system.

Given all of the above, caregiver health literacy can be key to the health of informal caregivers. One of the most recent definitions of health literacy refers to a person’s ability to access, interpret, and apply information and knowledge appropriately in order to preserve and promote their health, taking into account both their personal situation and the health system environment [15], thus including the knowledge, processing, and utilisation of information and the capacity to self-manage it. Numerous studies have shown that there is low health literacy in the adult population [16], as well as in caregivers of people with dementia [17]. This is especially important, as poor health literacy can have a negative impact on the quality of care provided, as caregivers do not have a good understanding of medical concepts or health recommendations and may not apply them correctly. Moreover, it also has an impact on the caregiver themselves, as health literacy has been shown to be related to caregiver burden, health-related quality of life, and time spent on care [18]. In this regard, it is also relevant to consider the factors that influence health literacy, as older age, in particular being over 65 years old, is often considered to be an important factor, but it is a lower educational or socioeconomic status that is generally associated with lower health literacy [19].

Specifically, in relation to physical activity, previous studies have shown that informal carers of people with dementia are more likely to report substantial physical difficulties in providing care to their beneficiaries compared to carers of people without dementia, and that when care is provided to their spouses, they are significantly more likely (41%) than other co-spousal carers of a similar age to become increasingly frail during the time between becoming carers and the death of their spouse [20,21].

Thus, physical activity could play a crucial role, as the benefits of physical activity for the adult population, both physically and mentally, are well known. However, until a few years ago, there was no evidence on the specific benefits that physical activity could have specifically on informal caregivers of people with dementia, but more and more recent studies have looked at how physical activity affects this population. In 2023, da Silva-Sauer et al. [22] found that there was a significant association between physical activity restriction, increased somatic symptoms, and increased caregiving burden among informal caregivers, particularly with regard to cardiovascular complaints. The researchers emphasised the importance of addressing caregivers’ sedentary lifestyles and promoting exercise to improve their health and quality of life. Consequently, physical activity interventions could have a beneficial effect on caregivers’ psychosocial aspects and physical activity levels, with caregivers themselves stating that physical activity can be an important element in their emotional health, physical well-being, and social connectedness [23].

The inclusion of technologies as a means of developing PA and health interventions could be very effective, as a growing body of scientific evidence supports the effectiveness of technology-based interventions for improving health and well-being [24,25,26], being generally effective in improving depressive symptoms, perceived stress, anxiety, and self-efficacy in family caregivers of people with dementia and having potential benefits for those receiving care [24]. Digital interventions provide numerous advantages, such as (a) high accessibility, being able to be used at any time and any place; (b) flexibility, adapting to the individual needs and preferences of each caregiver; (c) interactivity, offering interactive content, such as videos, games, and quizzes, to facilitate learning; and (d) personalisation, adapting to the physical levels and emotional state of each caregiver, as well as recommending personalised resources based on the caregiver’s needs or time.

To the best of our knowledge, there have been studies that intervened through psychoeducational [27,28] or cognitive–behavioural [29,30] programmes for caregivers of people with dementia or publications on didactic exercise interventions in people with dementia and their caregivers [31,32], as well as some educational, psychoemotional, and physical interventions whose medium of application was the internet [24]. In addition, there is evidence that programmes including educational modules, forums and real-time support sessions [33], and eHealth psychoeducational programmes aimed at increasing knowledge of neurocognitive disorders, their management at home, and the presence of national support services [34] have significantly reduced the level of behavioural symptoms in patients with dementia, increased empowerment, and eased the burden on caregivers, thus improving their caregiving skills. There are even interventions that have evaluated the effectiveness of an online psychoeducational programme combined with an immersive virtual reality (VR) experience in reducing caregivers’ perceived stress by acting on the cognitive and affective components of empathy [35]. However, there is no study that has used technological means to carry out an interdisciplinary programme with PA interventions together with health literacy for informal caregivers of people with dementia. Therefore, the aim of this project is to determine the effect of an 8-week intervention programme based on the CAREFIT (Caregivers’ Active Resilience & Exercise for Fitness and Well-being) programme on the HRQoL and psychoemotional health (stress, anxiety, depression, and perceived social support and caregiver burden) of caregivers of people with dementia.

In this sense, the hypothesis of the study protocol is that the implementation of an 8-week intervention programme based on the CAREFIT model will improve health-related quality of life (HRQoL) and psychoemotional health indicators (decreased stress, anxiety, depression, and overload, as well as increased perceived social support) in caregivers of people with dementia, compared to those who do not participate in the programme.

